**Method:**

This prospective cohort study will recruit at least 328 women through healthcare institutions providing reproductive and perinatal care. Eligible participants will include non-pregnant women, pregnant women, and women within the first year postpartum. Where feasible, partners of enrolled women will also be included to provide complementary dyadic data. Participants will be followed from baseline to 3, 6, and 12 months. Data will be collected through web-based questionnaires and routine clinical records. No experimental intervention will be delivered, and participation in the study will not modify standard clinical care. Repeated measures will capture mental health, reproductive intentions and behavior, war-related and perinatal experiences, and key sociodemographic and obstetric characteristics. Primary analyses will use mixed-effects models to examine mental-health trajectories, with reproductive status modeled both as a baseline cohort characteristic and, where participants change status during follow-up, as a time-varying covariate; reproductive transitions will also be examined as secondary longitudinal outcomes.

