#### Sample size

2.2.1

The sample size was estimated for the primary longitudinal mixed-model repeated-measures analysis, with the World Health Organization–Five Well-Being Index (WHO-5) score anchored as the primary outcome. Accordingly, the calculation was designed to provide adequate statistical power to detect differences in longitudinal WHO-5 trajectories according to war-related stress exposure. Sample size estimation was conducted in R (RRID: SCR_001905) using the *longpower* package (80). Parameter values were derived from previously published longitudinal studies, consistent with Harrall et al.’s recommendations (81). Given the substantial logistical and participant burden associated with data collection during an ongoing war, statistical power was set at 0.8, and the type I error rate was set at 0.05. Equal allocation across the two comparison levels specified in the power model was assumed.

The standard deviation of the WHO-5 outcome among postpartum women was set at 1.05, based on data reported by Mor et al. (82). The correlation structure was specified as a first-order autoregressive process with a correlation parameter of 0.38, informed by longitudinal data reported by Qandil et al. (83). Retention assumptions were based primarily on the cumulative follow-up pattern reported by Damtew et al. (84), with retention rates of 92.9% at 6 weeks, 84.2% at 6 months, and 73.0% at 12 months, calculated using the baseline cohort as the denominator at each follow-up. Although some studies in post-conflict settings have reported relatively high retention, such as the 77.3% 2-year retention reported by Silove et al. (85), the present assumptions were considered more appropriate for this study context.

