The final sample size calculation assumed a heterogeneous first-order autoregressive variance-covariance structure, four measurement occasions, and a two-sided test. Under these assumptions, the minimum required sample size was estimated at 328 participants. This sample size is expected to provide adequate power for detecting differences in longitudinal WHO-5 trajectories by war-related stressor exposure in the primary mixed-model repeated-measures analysis after accounting for attrition. The sample-size calculation was anchored to the WHO-5 score as the reference outcome for the primary longitudinal analysis in the women’s cohort. Secondary outcomes, for instance, reproductive-behavior outcomes, clinical outcomes, reproductive-status-by-time interactions, and the optional dyadic partner component will be analyzed where the available data structure, sample size, and model stability permit. These analyses will not be considered independently powered confirmatory tests; they will be interpreted as hypothesis-generating.

A sensitivity power analysis was also conducted using a more conservative compounded attrition scenario, assuming 85% retention per 3-month intervals up to the 12-month follow-up, to reflect the possibility of greater attrition in the wartime context. In this scenario, retention proportions were set at 1.00, 0.85, 0.72, and 0.52. Under this conservative attrition scenario, the planned sample size of N = 328 would provide approximately 70% power, which was considered relevant for a perinatal population in a wartime setting (86). To maintain 80% power under the same conservative retention assumptions, the required sample size would increase to approximately N = 416. Accordingly, the planned sample size should be interpreted as adequately powered for the primary longitudinal model under the main retention assumptions, whereas findings should be interpreted more cautiously if attrition approaches the conservative scenario. The corresponding R script is available in the project Open Science Framework (RRID: SCR_003238) repository (87).

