Item-level analyses will include inspection of response distribution and missingness, floor and ceiling effects, corrected item-total correlations, and score distributions. For measures administered at multiple assessment waves, longitudinal measurement invariance will be evaluated to assess whether the constructs are measured comparably over time. Invariance by respondent characteristics or reproductive status will be examined where item wording, sample size, and model stability permit. Configural, metric, and scalar invariance will be examined sequentially; partial invariance will be considered when full invariance is not supported (146).

The results of these analyses will inform the interpretation of scale scores, between-group comparisons, and longitudinal change estimates. If a translated scale demonstrates poor psychometric performance, substantive analyses using that scale will be reconsidered before interpretation. The research team will inspect item wording, response distributions, factor loadings, residual correlations, reliability estimates, and the effect of individual items on model fit and internal consistency. Depending on the source and extent of the problem, analyses may use theoretically justified subscale scores, conduct sensitivity analyses excluding items, or report the measure descriptively. Measures with inadequate reliability, unstable factor structure, or insufficient evidence of comparability across groups or time will not be used. Any deviations from the planned scoring approach will be reported transparently.

Primary outcomes will be analyzed using mixed-effects growth models with repeated observations nested within participants. Models will include fixed effects for time, war-related stress exposure, and the interaction between them. Time will initially be modeled as categorical; alternative specifications will be compared when empirically justified. Random intercepts will be used to estimate between-person differences in baseline symptom levels, and random slopes for time will be tested to capture heterogeneity in change over time. Model selection will be guided by likelihood-ratio tests, Akaike information criterion, Bayesian information criterion, convergence diagnostics, and variance estimates. The intraclass correlation coefficient will be estimated from unconditional models.

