Baseline reproductive status will be included to account for cohort-entry differences between non-pregnant, pregnant, and postpartum participants. In addition, reproductive status assessed at each wave will be modeled as a time-varying covariate when participants transition between reproductive states during follow-up. Where sample size permits, interactions between time, war-related stress exposure, and reproductive status will be examined to assess whether mental-health trajectories differ across reproductive stages. Primary longitudinal analyses will be conducted in the women’s cohort. Mixed-effects growth models will include repeated observations nested within participants and will estimate mental-health trajectories across the four assessment waves. Baseline reproductive status will be included as a cohort-entry characteristic to account for initial differences between non-pregnant, pregnant, and postpartum participants.

Reproductive transitions will also be examined as secondary longitudinal outcomes. Combining groups in this framework is justified because mixed-effects models allow unequal numbers of observations, time-varying covariates, and adjustment for baseline reproductive status. Transition variables will be derived between waves, including, where applicable, becoming pregnant, giving birth, having pregnancy or neonatal loss, entering the postpartum period, remaining in the same reproductive-status group, or other documented reproductive-status changes. Binary transitions will be analyzed using generalized mixed-effects models with a logit link, whereas transitions with more than two categories will be modeled using multinomial or alternative categorical longitudinal models, depending on event frequency and model stability. These analyses will be interpreted as secondary or exploratory if the number of observed transitions is limited.

Values resulting from planned non-administration of a measure (see **Table 3**) will be coded as structurally non-applicable and will be distinguished from missing data due to item nonresponse or loss to follow-up. Structurally non-applicable values will not be imputed or treated as participant-level missingness. Analyses of cohort-specific measures will therefore be restricted to the eligible reproductive-status group or wave, while mixed-effects models will use all available repeated observations for variables applicable across groups.

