For postpartum participants, time since childbirth will be incorporated into the analytic framework to account for heterogeneity within the first postpartum year. Postpartum timing will first be described continuously in months since childbirth and, where sample size permits, also examined using clinically meaningful intervals, such as early versus later postpartum periods. In longitudinal models, postpartum timing will be considered as an adjustment variable, a time-varying covariate, or a basis for sensitivity or stratified analyses, depending on the distribution of observations and model stability.

Adjusted models will include selected sociodemographic, obstetric, clinical, and contextual covariates. For time-varying predictors, person-mean centering will be used to distinguish within-person from between-person effects (147). Moderation by risk or protective factors, such as displacement status, prior mental health history, socioeconomic status, social support, and reproductive status, will be tested using interaction terms. Results will be reported as model-based estimates with 95% confidence intervals, p-values, standardized effect estimates, marginal and conditional R², estimated marginal means, contrasts, and predicted trajectory plots. Interpretation will prioritize effect sizes, clinical relevance, and robustness across sensitivity analyses.

To reduce the risk of false-positive findings and model overfitting, the primary analytic model will follow a prespecified hierarchy. The primary longitudinal analysis will focus on WHO-5 trajectories, with baseline war-related stressor burden as the main exposure and the stressor burden-by-time interaction as the principal test of the primary hypothesis, with baseline-to-12-month change treated as the principal longitudinal contrast. Baseline reproductive status will be included to account for cohort-entry differences. Data-driven stepwise selection will not be used for primary inference. For tests conducted across the primary outcome family, Holm-adjusted p-values will be reported alongside unadjusted estimates.

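### As written, the baseline-status adjustment cancels out of the primary change contrast, and the text conflicts on whether wave-updated status belongs in the primary model

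*Protocol article*

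**What the plan says.** Section 2.5 of the protocol article makes the burden-by-time interaction on WHO-5 the principal test, with change from baseline to 12 months as the principal contrast. Burden is counted at baseline (section 2.4.1.1).

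On the model terms, section 2.5 states: "Models will include fixed effects for time, war-related stress exposure, and the interaction between them". It then adds the cohort at entry: "Baseline reproductive status will be included to account for cohort-entry differences". An earlier paragraph of the same section gives the purpose as handling initial differences between the three cohorts. Interactions involving time, burden and status are to be examined only if the sample allows, and section 2.2.1 lists status-by-time interactions among the analyses that are not independently powered and only generate hypotheses.

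On status after baseline, section 2.5 says: "reproductive status assessed at each wave will be modeled as a time-varying covariate when participants transition between reproductive states during follow-up". The Abstract places this in the primary analyses, "with reproductive status modeled both as a baseline cohort characteristic and, where participants change status during follow-up, as a time-varying covariate". The paragraph of section 2.5 that sets out the primary hierarchy names baseline status only.

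**The concern.** A covariate fixed at baseline and entered without a time interaction adjusts the level of WHO-5, not its change. The primary test concerns change. If cohorts differ both in burden and in their natural course over the year, part of the ordinary perinatal course is read as a burden effect. The protocol itself expects different courses: the second hypothesis in the Introduction links reproductive status to trajectories. Women may enter at any gestation (section 2.2.2), so those pregnant at entry will generally have left that pregnancy by the 12-month wave.

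Wave-updated status raises a different problem. It is measured after the exposure, and the Introduction argues that war disruption may affect reproductive decisions and planning. Conditioning on it can remove or distort whatever part of the burden effect acts through conception or loss. The two descriptions of the primary model therefore estimate different quantities, and the text does not settle which one is the principal test.

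**Working it through.** **Inputs from the protocol.** Section 2.2.1: "statistical power was set at 0.8, and the type I error rate was set at 0.05"; "four measurement occasions, and a two-sided test"; "The standard deviation of the WHO-5 outcome among postpartum women was set at 1.05"; "first-order autoregressive process with a correlation parameter of 0.38"; retention 1, 0.929, 0.842, 0.730; N = 328. Cohort differences in burden or in change are not given. Every such value below is an assumption.

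**1. The plan's own figures.** N = 328 cannot be rebuilt because the article states no effect size. The conservative pair is self-consistent: (1.960 + 0.842)/√(416/328) − 1.960 = 0.528, and Φ(0.528) = 0.701, against the stated 70%. This does not bear on the point, but it supports taking 80% at N = 328 as the starting power in step 5.

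**2. Cancellation.** For woman i at wave j, with burden B, status S and a person effect u:

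Y_ij = α + τ_j + βB_i + γ_jB_i + δS_i + u_i + e_ij, with γ_1 = 0.

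Y_i4 − Y_i1 = (τ_4 − τ_1) + γ_4B_i + (e_i4 − e_i1).

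δ is gone. With complete data the estimate of γ_4 equals the regression of Y_4 − Y_1 on B, with or without the status term. In simulation the two differed by at most 2e-16 SD. With the planned retention, single runs differed by at most 0.026 SD and mean bias was unchanged (0.054 against 0.054 SD).

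**3. Size of the leftover confounding, true burden-by-time effect zero.**

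(a) N = 328, SD 1.05, AR(1) 0.38, main retention, 600 runs per setting, status as a main effect:

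| Burden shift (SD) | Difference in 12-month change (SD) | Bias (SD per SD of burden) | Rejection |
|---|---|---|---|
| 0.3 | 0.3 | 0.0125 | 4.0% |
| 0.3 | 0.6 | 0.028 | 7.7% |
| 0.6 | 0.3 | 0.028 | 7.7% |
| 0.6 | 0.6 | 0.054 | 12.0% |

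A burden shift of 0.6 with no difference in change gave 5.2%. With status by wave, the last three rows of the table gave 5.0%, 5.8% and 7.0%, and bias in the last row fell to −0.003. Simulation error is about 1 point, so 7.0% is about two errors above 5%.

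(b) On the 0–100 scale, assuming SD 21, equal thirds, 73% retained, and one cohort with higher burden and a lower 12-month change, 4,000 runs per setting:

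| Burden gap (domains) | Change gap (points) | Rejection, as written | With status by time |
|---|---|---|---|
| 0.5 | 8 | 6.7% | 5.4% |
| 0.5 | 12 | 8.1% | 4.7% |
| 1.0 | 8 | 10.3% | 4.3% |
| 1.0 | 12 | 17.5% | 5.7% |

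Bias at a one-domain gap was −0.94 and −1.39 points per domain.

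Hand check of the third row. Bias = p(1 − p) × burden gap × change gap / Var(B). With p = 1/3, 0.222 × 1 × 8 / Var(B) = 0.94 implies Var(B) = 1.89. Variance of change is 2 × 21² × (1 − 0.38³) = 834; women at 12 months, 0.73 × 328 = 239. SE = √(834/(239 × 1.89)) = 1.36 and bias/SE = 0.69. Rejection = Φ(−1.96 + 0.69) + Φ(−1.96 − 0.69) = 0.106, in line with 10.3%.

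**4. Wave-updated status.** Suppose burden acts only through conception (odds ratio 0.7 or 0.5 per SD of burden, pregnancy effect ±0.5 SD). The total 12-month effect is then about 0.05 or 0.09 to 0.10 SD in absolute size, and conditioning on wave status reduces it to about 0. With an unmeasured common cause of transition and outcome, conditioning leaves +0.013 to +0.020 SD. With an odds ratio of 1, conditioning does no harm. The person-mean centering planned for time-varying predictors would bring later waves into the covariate.

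**5. Cost of status by wave.** Parameters: (3 − 1) × (4 − 1) = 6. If status explains a share R² of burden variance, the N needed is 328/(1 − R²) and power at 328 is Φ(2.802√(1 − R²) − 1.960):

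| R² (assumed) | Power at 328 | N for 80% |
|---|---|---|
| 0.02 | 79.2% | 335 |
| 0.06 | 77.5% | 349 |
| 0.10 | 75.7% | 365 |
| 0.20 | 70.7% | 410 |

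In the one-domain setting of step 3(b), R² = 0.222/1.89 = 0.12, so N is about 372 and power about 75%.

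**The case against.** The text never says that status enters as a main effect only. This is a condensed article, status interactions are foreseen where the sample allows, and adjusted models with theory-chosen covariates are planned. That stands as a caution about wording. It does not remove the point, because section 2.2.1 positively assigns status-by-time to the hypothesis-generating analyses, and the stated purpose of the baseline term concerns levels at entry.

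A reader might infer that the two problems add up. They do not, because they belong to alternative models. If the primary hierarchy governs, wave-updated status is outside the principal test and what remains is a conflict of wording. If the Abstract governs, wave status may absorb some of the cohort-specific course.

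A reader might also infer that any use of wave status biases the result. For women pregnant at entry, the move to postpartum is set largely by gestational age at baseline, so the harm falls mainly on conception and loss. Nor does the protocol claim that stressors shape transitions: the Introduction sets out to examine this, and causal inference is disclaimed in sections 2.1 and 3.2.

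Finally, the inflation figures rest on inputs absent from the protocol, and the mildest settings show none. That is correct and limits the claim.

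**Conclusion.** The point holds in a bounded form. For the model as described, adjusting for baseline status does not protect the baseline-to-12-month burden contrast from confounding by cohort. The cancellation is algebraic, exact with complete data and nearly exact under the planned attrition. Whether it matters depends on two unknowns, the cohort differences in burden and in 12-month change. Under the null, rejection is about 4 to 5% if these are small, 7 to 8% in intermediate settings, and 10 to 17% if both are large. The documents do not support saying that the primary result will be biased, only that the stated adjustment would not prevent it.

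The disagreement between the Abstract, the time-varying paragraph of section 2.5 and the primary hierarchy is real and leaves the estimand of the principal test open. The loss from conditioning on wave status requires burden to affect conception or loss. The change should be made before data are seen.

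**What to change.** In the primary WHO-5 model of section 2.5, add baseline reproductive status by wave (6 degrees of freedom) as an adjustment. State in section 2.2.1 that this term serves as adjustment and needs no power of its own, while tests of whether trajectories differ by status stay hypothesis-generating. Keep wave-updated status out of the primary model and use it in secondary or sensitivity analyses. Align the Abstract and the time-varying paragraph of section 2.5 with the primary hierarchy.

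The change is one of wording plus a small to modest loss of precision. From 80% at N = 328, power falls to about 79% if status explains 2% of burden variance, 76% at 10% and 71% at 20%. The loss is largest where cohort and burden are most entangled, which is also where the unadjusted contrast is least trustworthy. Nothing here requires wave interactions for every other confounder or for recruitment site; that was neither tested nor costed.

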### Data analysis

2.5

Analyses will be conducted in R (RRID: SCR_001905) using longitudinal modeling approaches. The primary analytic aim is to estimate trajectories in prespecified primary mental health outcomes and to test whether trajectories differ by war-related stress exposure. The main exposure will be cumulative war-related stress exposure, derived from predefined ACT-PNM domains, including displacement, family separation, disruption of healthcare access, economic hardship, and direct or indirect exposure to threat. In primary mixed-effects models, war-related stressor exposure will be represented by baseline ACT-PNM-derived stressor burden, and the main test of the study hypothesis will be the interaction between stressor burden and time in predicting trajectories of the primary mental-health outcome family. The primary trajectory contrast will be the war-related stress exposure-by-time interaction across baseline, 3-month, 6-month, and 12-month assessments, with baseline-to-12-month change treated as the principal longitudinal contrast. Secondary aims will examine reproductive intentions, pregnancy planning, reproductive-status transitions, and cohort-specific perinatal outcomes. Exploratory analyses will examine dyadic partner data, sexual attitudes, domestic-violence myth acceptance, and clinician-recorded obstetric, maternal, fetal, and neonatal indicators.

Before analysis, the dataset will be checked for completeness, duplicate submissions, invalid response categories, incompatible units, out-of-range values, inconsistent reproductive status, and temporal inconsistencies between key clinical events. Examples of such inconsistencies include delivery dates preceding pregnancy-related assessments, postpartum status recorded before childbirth, gestational age values outside plausible ranges, or incompatible pregnancy outcome categories. Values will not be reconstructed from other variables unless the derivation rule has been specified in advance.

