Other mental-health outcomes, reproductive-behavior outcomes, reproductive-status transitions, partner-reported variables, clinical indicators, and contextual measures will be examined as secondary or exploratory analyses according to their role in the analytic framework. These models will be specified with attention to the available sample size, distribution of observations, number of parameters, convergence, and precision of estimates. Where model instability or sparse data are evident, simpler specifications or descriptive presentation will be used. Secondary outcomes will be interpreted as supportive analyses, and exploratory or contextual measures will be interpreted as hypothesis-generating.

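### The protocol names both WHO-5 alone and a Holm-adjusted family of mental-health outcomes as primary, and the stated 80% power is secured only if WHO-5 is tested alone at 0.05

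*Protocol article*

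**What the plan says.** Statements that make WHO-5 the single primary outcome:

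- Section 2.2.1 (Sample size) anchors the calculation to WHO-5 as the primary outcome. There, "statistical power was set at 0.8, and the type I error rate was set at 0.05", with "four measurement occasions, and a two-sided test". On that basis "the minimum required sample size was estimated at 328 participants".
- Section 2.5 (Data analysis), in the paragraph on the hierarchy: "The primary longitudinal analysis will focus on WHO-5 trajectories". The stressor burden-by-time interaction for WHO-5 is named there as the principal test of the primary hypothesis.

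Statements that make a family primary:

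- The first hypothesis, at the end of the Introduction, is worded for a primary family of mental-health outcomes.
- Section 2.4.2 (Primary outcome measures) lists five instruments: WHO-5, EPDS, City BiTS, GAD-7 and SCI-2-SF.
- The opening paragraph of section 2.5 describes the main test of the study hypothesis as the interaction of burden with time "in predicting trajectories of the primary mental-health outcome family".
- The growth-model paragraph of section 2.5 speaks of primary outcomes in the plural.

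The multiplicity rule, at the end of the hierarchy paragraph: "For tests conducted across the primary outcome family, Holm-adjusted p-values will be reported alongside unadjusted estimates".

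The closing paragraph of section 2.5: "Other mental-health outcomes, reproductive-behavior outcomes, reproductive-status transitions, partner-reported variables, clinical indicators, and contextual measures will be examined as secondary or exploratory analyses".

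**The concern.** These statements lead to different decision rules. Under section 2.4.2, EPDS, City BiTS, GAD-7 and SCI-2-SF are primary; under the end of section 2.5 they are not. If the end of section 2.5 governs, the primary family has one member and the Holm step does nothing. If section 2.4.2 governs, WHO-5 sits inside a Holm family, and the sample size, calculated at an unsplit 0.05, does not match the test.

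The protocol reports adjusted and unadjusted results side by side and does not say which one decides. The same WHO-5 result could then be read as positive or negative according to which sentence is followed, and that choice would be open after the data are seen.

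**Working it through.** **Inputs.** From section 2.2.1: power 0.80, two-sided type I error 0.05, N = 328 under the main retention assumptions; about 70% power at N = 328, and N = 416 for 80%, under the conservative attrition scenario. From section 2.4.2: five instruments, so m = 5. This is a count of the subsections; the text never states the family size.

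**The plan's own figure.** N = 328 cannot be rebuilt from the article, because it gives neither the effect size nor the visit-specific standard deviations. The check does not need them: 80% power at two-sided 0.05 fixes the expected value of the test statistic at

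z(0.975) + z(0.80) = 1.960 + 0.842 = 2.802.

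The plan's two conservative-scenario figures agree with each other on this basis: 2.802 × √(328/416) = 2.488, and Φ(2.488 − 1.960) = 0.701, the stated 70%.

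**Power for WHO-5 at one Holm step.** With m hypotheses still in play, the threshold is 0.05/m and power = Φ(2.802 − z(1 − 0.05/(2m))).

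| m | Two-sided level | Power for WHO-5 |
|---|---|---|
| 1 | 0.05 | 80% |
| 2 | 0.025 | 71.2% |
| 3 | 0.0167 | 65.8% |
| 4 | 0.0125 | 61.9% |
| 5 | 0.01 | Φ(2.802 − 2.576) = 58.9% |

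The last row is the floor for m = 5, reached when no other outcome is rejected ahead of WHO-5. The ceiling is 80%, because Holm never rejects a hypothesis whose unadjusted p-value exceeds 0.05.

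**Full Holm procedure.** Simulation of five tests (400,000 replicates per setting, common correlation 0 to 0.7) gave WHO-5 power of about 59% if the other four outcomes have no effect, and 68% to 70% if all five have 80% marginal power.

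**Sample size.** Holding 80% power at the 0.01 step under the main retention would need 328 × ((2.576 + 0.842)/2.802)² ≈ 488 women.

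**Conservative attrition.** Where the plan itself expects 70% power, first-step power would be Φ(2.488 − 2.576) = 46.5%.

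**Decision example.** If WHO-5 has p = 0.03 and this is the smallest of the five, Holm gives 5 × 0.03 = 0.15. If it is not the smallest, the multiplier is lower, down to 1 for the largest, subject to the earlier steps having been passed.

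**The case against.** The strongest reply is that the text leans toward one reading. WHO-5 anchors the sample size, and section 2.5 sets out a hierarchy with the WHO-5 interaction as the principal test. On that reading WHO-5 keeps its 0.05 and its 80% power. The Holm sentence can be taken as a reporting statement only, the study is observational, and interpretation is meant to rest on effect sizes and robustness more than on p-values. A separate analysis plan might also fix the family's membership and the deciding p-value.

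Much of this stands. It supports WHO-5 as the intended primary outcome and makes the power loss conditional. It does not remove the contradiction, which lies in what the protocol states and not in what it omits: the hypothesis, the heading of section 2.4.2 and the opening of section 2.5 all still say family, and Holm runs across a family that, by that heading, contains WHO-5. The qualifier in the closing paragraph of section 2.5, that outcomes are handled according to their analytic role, does not say which role the other four have.

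Three stronger readings are tempting, and the document does not support them.

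- A reader might infer that the study simply has 59% power. That needs Holm to govern, five members, and no other outcome rejected first.
- A reader might infer a family-wise error rate of 1 − 0.95⁵ = 22.6%. That needs any one of five independent outcomes to carry the claim at its unadjusted p-value. No passage allows this, and overlapping distress scales in the same women are unlikely to be independent.
- A reader might infer from Table 3 that the family cannot be tested, because EPDS is not scheduled for the non-pregnant cohort and City BiTS is scheduled only for the postpartum cohort. Section 2.5 already restricts cohort-specific measures to the eligible group, and Holm needs valid p-values, not identical samples. These tests can be run, though not on all 328 women.

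**Conclusion.** The point holds as a contradiction in the current text. The protocol names both WHO-5 alone and a family as primary, applies Holm across the family without naming the deciding p-value, and plans the sample size as if WHO-5 stood alone.

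The stated 80% is secured only if WHO-5 is tested alone at two-sided 0.05. If Holm-adjusted p-values over the five listed instruments govern, WHO-5 power is between 58.9% and 80%, and about 68% to 70% if all five have equal 80% marginal power. These figures rest on the plan's own design effect and main retention, a normal approximation for the principal contrast, and a family of five counted from section 2.4.2.

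**What to change.** State that WHO-5 is the only primary outcome and that its burden-by-time interaction is tested at two-sided 0.05 without multiplicity adjustment. This follows the protocol's own sample size and hierarchy, and keeps 80% power at N = 328 under the main retention assumptions. Relabel EPDS, City BiTS, GAD-7 and SCI-2-SF as secondary mental-health outcomes, analysed in their eligible groups, and confine any Holm adjustment to those four. Align the wording in the Introduction's first hypothesis, the heading of section 2.4.2, and the opening, growth-model and hierarchy paragraphs of section 2.5.

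If the sponsor prefers a Holm-governed family of five, the protocol should say that the adjusted p-value decides and restate the WHO-5 power as 58.9% to 80%. Holding 80% at the first Holm step would take about 488 women, 160 more than planned.

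The first option costs only protocol wording, ideally before any outcome data are examined, and needs no extra data.
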